|                                                      |                                                                                                                                                                                                                                                                                                                                                                                                                                                                                                                                                                                                                                                                                                                                                                                                                                                                                                                                                                                                                                                                    |
|------------------------------------------------------|--------------------------------------------------------------------------------------------------------------------------------------------------------------------------------------------------------------------------------------------------------------------------------------------------------------------------------------------------------------------------------------------------------------------------------------------------------------------------------------------------------------------------------------------------------------------------------------------------------------------------------------------------------------------------------------------------------------------------------------------------------------------------------------------------------------------------------------------------------------------------------------------------------------------------------------------------------------------------------------------------------------------------------------------------------------------|
|                                                      | 
 
- Other circumstances judged by investigators that are not suitable for this clinical trial.
 
                                                                                                                                                                                                                                                                                                                                                                                                                                                                                                                                                                                                                                                                                                                                                                                                                                                                                                                     |
| Subject's early withdrawal                    | 
Early withdrawal means that the subject fails to complete the vaccination and blood collection procedures in accordance with clinical study protocol, and investigator decides whether to continue the follow-up related research according to the situation. When any of the following conditions occur, the subject will withdraw from the clinical trial in advance.
 
 
- The subject requests to withdraw from the clinical trial;
 
- Intolerable adverse events, whether related to the investigational drug or not;
 
- The health status of the subjects does not allow them to continue to participate in this trial;
 
- The subjects are vaccinated with other clinical investigational vaccines during the study period;
 
- Any other reason that investigator considers.
 
                                                                                                                                                                                    |
| Criteria for suspension and early termination | 
In case of any of the following circumstances, the trial shall be suspended, and the investigator, the sponsor and the Ethics Committee shall jointly hold a meeting to decide whether to terminate the clinical trial early:
 
 
- The number of subjects with adverse reactions of severity Grade 3 or above exceeds 15% of the subjects vaccinated in this subgroup;
 
- One case of Grade 4 adverse reaction related to vaccination or SUSAR has occurred.
 
 
In case of any of the following circumstances, the clinical trial shall be terminated early:
 
 
- Sponsor has found that the vaccine has potential safety hazards or the trial has quality related problems, and requiring the complete termination of the study.
 
- The Ethics Committee requests the termination of the trial because of the violation of ethics in the trial.
 
- Request by the administrative authority to terminate the trial.
 
 |
| Trial End point                               | 
Immunogenicity endpoint:
 
Primary endpoint:
 
GMT and the 4-fold rise of anti-SARS-CoV-2 neutralizing antibody 14 days after sequential vaccination of one booster dose;
 
GMT and 4-fold rise of anti- SARS-CoV-2 neutralizing antibody 28 days after sequential
                                                                                                                                                                                                                                                                                                                                                                                                                                                                                                                                                                                                                                                                                                                                                             |

vaccination of one booster dose.

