### **4.6.2 Blinding**

Before the start of the study, the staffs from sponsor who will not participate in the clinical trial will blind the vaccines to be used in the study together with the unblinded randomization statistician. The vaccine label will be stucked on the specified position of each vaccine according to vaccine randomization list. The randomization statistician will supervise and guide the process of blinding. After blinding is completed, the vaccine randomization list will be sealed by the unblind randomization statistician. The whole blinding process will be recorded and written in a

document named blinding records, which is one of the important documents of this trial. The blinding personnel cannot participate in other related works of the trial, and they are not allowed to tell any information to any personnel who participates in the trial.

The subject randomization list and vaccine randomization list will be sealed, including randomization number, vaccine number and the corresponding group assignment, together with the randomization seed number. They will be well sealed and saved until the database is locked.

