#### **4.6.3 Emergency Blind Code Breaking**

In an emergency, when the investigator thinks that the group assignment information of one subject is beneficial for the handling of adverse events, it will be broken through the Emergency Blind Code Breaking Module in IWRS. The investigators need to discuss with the Sponsor and both shall reach agreement before performing emergency blind code breaking.

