#### **5.1.4 Criteria for Clinical Trial Suspension and Termination**

In case of any of the following circumstances, the clinical trial shall be suspended or terminated, and the investigator, the sponsor and the ethics committee shall jointly decide whether to terminate the clinical trial in advance:

- After vaccination, the number of subjects with adverse reactions with severity of Grade 3 exceeds 15% of the number of subjects vaccinated in this subgroup.
- One case of Grade 4 adverse reaction or SUSAR was confirmed to be related to vaccination.

In case of any of the following circumstances, the clinical trial shall be terminated:

- The Sponsor found that the vaccine has potential safety hazard, or the study has quality problems and requires the complete termination of the trial.
- The Ethics Committee requests termination of the trial because of the ethical violation in the study.
- The administrative authority requests termination of the trial.

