## 7.6 Criteria for Suspension or Early Termination

**In case of any of the following circumstances, the trial shall be suspended, and the investigator, the sponsor and the Ethics Committee shall jointly hold a meeting to decide whether to terminate the clinical trial early:**

- One case of Grade 4 adverse reaction related to vaccination or SUSAR in any group, including death or life-threatening SAE;
- The number of subjects with adverse reactions of severity Grade 3 or above

---

exceeds 15% of the subjects vaccinated in this subgroup;

- DSMB evaluation of clinical research has high potential safety risks.

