## **8. SAFETY DEFINITION, REPORTING AND MONITORING**

### **8.1 General Precautions**

This clinical trial is a randomized, double-blind and controlled trial design.

Before the start of the trial, the sponsor shall strictly examine the trial site in accordance with GCP requirements, focusing on whether the environmental facilities of the trial site meet the requirements of "Vaccination Management Standards" and "Guiding Principles for Quality Management of Vaccine Clinical Trials". Ensure the first aid facilities and first aid equipment in the first aid room are complete and effective, and the first aid doctors have corresponding qualifications and capabilities. Emergency related personnel (emergency doctors, emergency nurses, ambulance drivers, etc.) are trained to be qualified and familiar with the transfer routes and procedures of the agreed hospital. They are on standby at the trial site during vaccination. The trial site shall be equipped with ambulances. The ambulance shall be parked in a fixed position to keep the vehicle in good condition and in an emergency and shall be under the command and transfer of the emergency response team at any time. During the vaccination period, the agreement hospital will make daily preparations for medical personnel, instruments and equipment, first aid drugs and first aid sites to ensure that the subjects can receive timely treatment. The trial site shall formulate an emergency plan, stipulate personnel responsibilities, contact numbers, rescue routes and other measures to ensure timely handling of unexpected adverse events, and ensure effective contact between subjects and investigators so that any adverse events can be reported and handled quickly.

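### The 15% Grade 3 suspension rule has an undefined denominator, and the protocol gives no route to counts by vaccine arm before database lock

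*Protocol*

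**What the plan says.** The rule appears three times. The Synopsis (criteria for suspension and early termination) suspends the trial if "The number of subjects with adverse reactions of severity Grade 3 or above exceeds 15% of the subjects vaccinated in this subgroup", after which "the investigator, the sponsor and the Ethics Committee shall jointly hold a meeting to decide whether to terminate the clinical trial early". Section 7.6 repeats this and adds a separate trigger: "DSMB evaluation of clinical research has high potential safety risks". Section 5.1.4 words the rule as "adverse reactions with severity of Grade 3 exceeds 15% of the number of subjects vaccinated in this subgroup", without the higher grades and without the DSMB trigger. None of the three defines the subgroup or says who counts. The only other use of the word that bears on this is the heading of section 10.4, which covers the three interval cohorts (1-3, 4-6 and at least 6 months after two doses).

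On blinding, section 8.1 states: "This clinical trial is a randomized, double-blind and controlled trial design". Section 4.6.2 says of the subject and vaccine randomization lists: "They will be well sealed and saved until the database is locked". Of the people who do the blinding it says that "they are not allowed to tell any information to any personnel who participates in the trial". The one earlier opening is in section 4.6.3: when the assignment of a single subject is needed in an emergency, "it will be broken through the Emergency Blind Code Breaking Module in IWRS". Section 9 puts lock and unblinding after the 28-day immunogenicity results and at least one month of safety follow-up. Section 10.5 plans no interim analysis.

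**The concern.** A rule on the rate of Grade 3 reactions is useful only if someone can count the right subjects while vaccination is still going on. Each subject receives one dose, and adverse events are collected for 30 days after it. Allocation is opened in bulk only after that window has closed for everyone. During enrolment the protocol describes no way to attribute Grade 3 reactions to a vaccine, apart from breaking the code one subject at a time.

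What the rule can detect therefore depends on a word that the protocol leaves undefined. On one reading the count cannot be made at all. On the other it can be made, but it responds weakly when only one vaccine is reactogenic and the other is not.

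**Working it through.** **Inputs from the protocol.** Threshold: more than 15% (Synopsis, 5.1.4, 7.6). Allocation 1:1, 300 per arm in each of three cohorts, so 600 per cohort and 3 × 600 = 1,800 in total (4.2, 10.1). The protocol gives no derivation for the 15%, so there is no figure of its own to reproduce.

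**Assumed inputs.** The protocol gives no Grade 3 rate for either vaccine. The test-arm rate is set at 20% for illustration, and the control rate is varied over 2%, 5% and 10%.

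**The two readings against section 4.6.2.**

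- Subgroup = one arm of one cohort. More than 15% of 300 means 46 or more subjects (0.15 × 300 = 45). The count needs allocation, which is sealed until lock, and no exception is described.
- Subgroup = interval cohort. More than 15% of 600 means 91 or more subjects (0.15 × 600 = 90). The interval is known at enrolment, so the count can be made under the blind.

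**What averaging does.** At 1:1 the pooled rate is (pT + pC)/2, where pT and pC are the test and control rates. The pooled excess over control is (pT + pC)/2 − pC = (pT − pC)/2, which is always half the true excess. The pooled rate itself is half of pT only when pC = 0. With pT = 20% it is 11%, 12.5% and 15% at control rates of 2%, 5% and 10%. For the pooled rate to equal 15%, pT must be 30% − pC, that is 28%, 25% and 20%.

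**Probability that the count exceeds 15%.** Arm count: P(X ≥ k), X binomial(n, pT). Pooled count: P(X + Y ≥ m), with Y binomial(n, pC) and independent. For n = 50 per arm, k = 8 (more than 7.5) and m = 16 (more than 15). For n = 300, k = 46 and m = 91. Each probability is for a single look at that size, with pT = 20%.

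| Subjects per arm | Arm count | Pooled, control 2% | Pooled, control 5% | Pooled, control 10% |
|---|---|---|---|---|
| 50 | 0.81 | 0.07 | 0.17 | 0.43 |
| 300 | 0.98 | 0.0007 | 0.027 | 0.47 |

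The row for 50 per arm matters more in practice. At 300 per arm everyone in the cohort has already been vaccinated, so suspension can no longer protect anyone in it. The gap closes as the arms converge: at 300 per arm with control at 15%, the pooled count crosses with probability 0.94.

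**The case against.** The strongest reply is that the rule may already be complete. Section 10.4 applies the word subgroup to the interval cohorts. On that reading the 15% is a cohort rate, it can be counted under the blind, and nothing is lost against the stated rule. A reader might infer that the test arm must reach nearly twice the stated rate before suspension. That measures the rule against an arm threshold that the protocol does not clearly state. This part of the reply stands. What remains is that the denominator is undefined and that the operable reading is insensitive to a signal in one arm.

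A reader might also infer that sites are forced to count the arms together. No section assigns the count to sites, and section 8.3 makes the sponsor chiefly responsible for monitoring safety information. It would also be too strong to say that nobody could ever obtain counts by arm. The lists are loaded into the IWRS (4.6.1), section 7.6 names a DSMB without saying what it sees, and a charter or analysis plan may address access. But the sealing in section 4.6.2 is fixed in the protocol with no exception for the DSMB, so a charter that granted access would sit uneasily with the text.

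Other protections exist. A single related Grade 4 reaction or a SUSAR triggers suspension, the DSMB can trigger it, and section 7.3.1 requires a face-to-face visit within 24 hours of a known Grade 3 event. These limit the harm, but none is a rate rule for Grade 3 reactions.

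Counting by arm also has a price. With 25 per arm, a true rate of 10% exceeds 15% (4 or more subjects) about 24% of the time by chance. That is one reason not to prescribe the denominator here.

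**Conclusion.** The point holds as an undefined denominator combined with a blinding rule that leaves no described route to counts by arm before lock. Under the arm reading the rule cannot be operated as written. Under the cohort reading it can, but the excess over control is halved. For a true test-arm rate of 20%, the chance of crossing 15% at 50 per arm is then 0.07 to 0.43 for control rates of 2% to 10%, against 0.81 for a count in the test arm alone.

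The size rests entirely on assumed rates. It is large if the control vaccine causes few Grade 3 reactions and small if the two vaccines are similar. A reader might conclude that pooling dilutes a signal by half. That is exact for the test-arm rate only if control is 0%, and the protocol gives no control rate. Nor should 0.0007 against 0.98 be taken as the typical contrast: it belongs to a fully vaccinated cohort at the low control rate of 2%.

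**What to change.** Reconcile the Synopsis, section 5.1.4 and section 7.6 with section 4.6.2 by stating what the subgroup is and who counts it. In the same edit, resolve the difference between Grade 3 and Grade 3 or above, and the presence of the DSMB trigger in section 7.6 only.

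Add to sections 4.6.2 and 7.6 an exception that lets an unblinded statistician outside study conduct give the existing DSMB counts of Grade 3 or above reactions by arm, while sites and sponsor stay blinded.

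The cost is a few sentences in an amendment and simple periodic tables. The small downside is a controlled unblinded path that must be kept separate from study staff. This takes no position on the 15% figure, on which denominator applies, or on the suspension decision itself.

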**Secondary endpoint:**

GMT of anti-SARS-CoV-2 IgG antibody, 4-fold rise, GMI, and proportions of neutralizing antibody titered  $\geq 1:16$ ,  $\geq 1:32$  and  $\geq 1:64$  before vaccination and 28 days after vaccination of the sequential booster dose.

**Immune persistence endpoint:**

Anti-SARS-CoV-2 neutralizing antibody and GMT of IgG antibody 3 months, 6 months, 9 months and 12 months after full course of immunization, and the proportions of neutralizing antibody titered  $\geq 1:16$ ,  $\geq 1:32$  and  $\geq 1:64$ .

**Safety endpoint:**

The incidence and severity of any adverse reactions/events within 30 minutes after vaccination;

The incidence and severity of solicited adverse reactions/events within 0-7 days after vaccination;

The incidence and severity of unsolicited adverse reactions/events within 8-30 days after vaccination;

The incidence of SAE and AESI observed after vaccination and up to 6 months after full course of immunization.

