**Table 1 Sample Size and Procedures of Clinical Trial**

| Sequential Vaccination Time of Recombinant Vaccine | Booster Immunization | Sequential Vaccine Group | Sample Size | Safety                                                                                                                                                    | Blood Collection Time Point                                                                         |
|-----------------------------------------------------------|-----------------------------|---------------------------------|--------------------|------------------------------------------------------------------------------------------------------------------------------------------------------------------|------------------------------------------------------------------------------------------------------------|
| 1-3 months after 2 doses                                  | 31-90 days (+14)            | Recombinant Vaccine             | 300                | Collect AEs within 0-7 days and 8-30 days after immunization with sequential booster dose, and SAEs up to 6 months following immunization with the booster dose. | Before the sequential dose ①14 days②, 28days③, 3 months④, 6 months⑤, 9 months⑥, 12 months⑦after sequential |
|                                                           |                             | Inactivated Vaccine             | 300                |                                                                                                                                                                  |                                                                                                            |
| 4-6 months after 2 doses                                  | 91-180 days (+14)           | Recombinant Vaccine             | 300                |                                                                                                                                                                  |                                                                                                            |

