**Table 1 Sample size and Procedures of Clinical Trial**

| Sequential Vaccination Time of Recombinant Vaccine | Booster Immunization | Sequential Vaccine Group | Sample Size | Safety                                                                                                                                                                                         | Blood Collection Time Point                                                                                                             |
|-----------------------------------------------------------|-----------------------------|---------------------------------|--------------------|-------------------------------------------------------------------------------------------------------------------------------------------------------------------------------------------------------|------------------------------------------------------------------------------------------------------------------------------------------------|
| 1-3 months after 2 doses                                  | 31-90 days                  | Recombinant Vaccine             | 300                | Collected solicited AEs within 0-7 days and non-solicited AEs within 8-30 days after immunization with sequential booster dose, and SAEs up to 6 months following immunization with the booster dose. | Before the sequential dose
①, 14 days②, 28 days ③, 3 months ④, 6 months ⑤, 9 months ⑥, 12 months ⑦after sequential vaccination of one dose. |
|                                                           |                             | Inactivated Vaccine             | 300                |                                                                                                                                                                                                       |                                                                                                                                                |

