## 4.5 Safety Observation Indicators and Grading Criteria

### 4.5.1 Safety Observation Indicators

#### (1) Adverse events collected in 0-7 days

Local adverse events: pain, induration, swelling, rash, redness and pruritis.

Systemic adverse events: fever, diarrhoea, constipation, dysphagia, anorexia, vomiting, nausea, myalgia(systemic), arthralgia, headache, cough, dyspnoea, systemic pruritis (no skin damage), abnormal skin mucosa, acute allergic reactions, fatigue, and dizziness

Other adverse events: any medical events other than the above mentioned during clinical studies, such as acute diseases, accidental injuries, etc.

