#### **10.3.4 Safety Evaluation**

Adverse events and serious adverse events will be coded using the Medical Dictionary for Regulatory Activities (MedDRA), and summarized by system organ class (SOC) and preferred term (PT). AEs will be summarized by solicited and unsolicited AEs as well. The treatment emergent adverse events (TEAEs) will be analyzed here. AEs occurring before vaccination will be listed.

All TEAEs, vaccine-related TEAEs, vaccine-unrelated TEAEs, Grade $\geq$ 3 TEAEs and vaccine-related Grade $\geq$ 3 TEAEs will be summarized by group. The frequency, subjects and percentage in each group will be reported. Fisher exact test will be used to compare the difference between the groups. The strat time and severity of TEAEs will be summarized. The vaccine-related TEAEs and vaccine-unrelated TEAEs will be listed.

All TESAE, vaccine-related TESAEs and vaccine-unrelated TESAEs will be summarized by group. The frequency, subjects and percentage in each group will be reported. Fisher exact test will be used to compare the difference between the groups. All TESAEs will be listed.

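### The Synopsis and Table 1 of Section 4.2 start the unsolicited-event window at day 8, which conflicts with Sections 4.3.2, 4.5.1 and 10.3.4 and would leave the named unsolicited incidence incomplete

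*Protocol*

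**What the plan says.** Two places tie the type of event to the time window.

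- Synopsis, safety endpoint. The early window is "The incidence and severity of solicited adverse reactions/events within 0-7 days after vaccination" and the later one is "The incidence and severity of unsolicited adverse reactions/events within 8-30 days after vaccination". Two further items stand beside them: "The incidence and severity of any adverse reactions/events within 30 minutes after vaccination", and "The incidence of SAE and AESI observed after vaccination and up to 6 months after full course of immunization".
- Section 4.2, Table 1: "Collected solicited AEs within 0-7 days and non-solicited AEs within 8-30 days after immunization with sequential booster dose".

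Four places do not.

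- Synopsis, Table 1, gives both windows with no split by type: "Collect AEs within 0-7 days and 8-30 days after immunization with sequential booster dose".
- Section 4.3.2 words the safety endpoint as the incidence of adverse reactions and events in each of the two windows, without restricting either window to a type.
- Section 4.5.1(1) lists the local and systemic terms collected in days 0-7 and then adds "Other adverse events: any medical events other than the above mentioned during clinical studies". Section 4.5.1(2) collects any medical event in days 8-30.
- Section 10.3.4 analyses treatment-emergent adverse events and adds that "AEs will be summarized by solicited and unsolicited AEs as well". It states no start day for either category.

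**The concern.** An unsolicited event is one that is off the prompted list, whenever it happens. The Synopsis and Table 1 of Section 4.2 instead make the category begin on day 8. Days 0-7 are the days nearest the dose, when an unexpected vaccine-related event is most plausible, and the unsolicited category exists to pick up such events.

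If the analyst follows the only windows the protocol attaches to the two categories, off-list events in days 0-7 have no proper place. They are either left out of the unsolicited summary or put into the solicited one, where they do not belong. Either way, the reported unsolicited incidence and severity would not describe what the trial recorded. Safety is a secondary objective (Section 3.2), so this endpoint will be reported by name.

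**Working it through.** No sample size, power or error rate is involved, so there is no arithmetic to reproduce. The check takes a non-serious event that is off the solicited list and not of special interest, and asks where the protocol counts it according to when it starts.

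| Onset | Synopsis endpoints | Table 1, Section 4.2 | Section 4.3.2 endpoint | Collected under 4.5.1 | All-event analysis, 10.3.4 |
|---|---|---|---|---|---|
| First 30 minutes | Yes (any-event item) | No | Yes | Yes | Yes |
| After 30 minutes to day 7 | **No** | **No** | Yes | Yes | Yes |
| Days 8-30 | Yes (unsolicited item) | Yes | Yes | Yes | Yes |

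**An example from the protocol's own lists.** Chills are not among the local or systemic terms in Section 4.5.1(1), nor among the events of special interest in Section 4.5.4, although the Appendix lists them as a symptom in its case definition. Take non-serious chills on day 1:

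1. They are not a solicited term, so the solicited days 0-7 endpoint does not take them.
2. They start before day 8, so the unsolicited endpoint does not take them.
3. They start after the first 30 minutes, so the immediate endpoint does not take them.
4. They are neither serious nor of special interest, so the six-month endpoint does not take them.
5. They are recorded as an other adverse event under Section 4.5.1(1), fall within the Section 4.3.2 endpoint, and enter the treatment-emergent totals in Section 10.3.4.

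**If the same event is serious or of special interest,** the Synopsis item running from vaccination to six months counts it, so it is not lost there.

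**What Section 10.3.4 compares.** Fisher's exact test is specified for all treatment-emergent events, for those related and unrelated to vaccine, for Grade 3 or above, and for related Grade 3 or above. None of these starts at day 8. The solicited and unsolicited summary is an addition to them and has no window of its own, so it must take one from the endpoint definitions. Those definitions disagree.

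**The case against.** The strongest reply is that nothing is lost. The events are collected, Section 4.3.2 counts them, and the between-arm tests in Section 10.3.4 include them. The Synopsis version of Table 1 has no split by type either. On this view the Synopsis wording is loose shorthand, and the labelling of off-list events in days 0-7 can be left to the statistical analysis plan.

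Most of this stands. It rules out three stronger readings that someone might take from the Synopsis alone.

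- *That the between-arm safety comparison omits days 0-7.* It does not: every test named in Section 10.3.4 is free of a day-8 start.
- *That total risk is understated in both arms.* It is not: the treatment-emergent totals include these events.
- *That about a quarter of unsolicited events is dropped, because days 0-7 are 8 of the 31 days from 0 to 30.* That ratio is a share of calendar days, not of events. The documents give no distribution of onset times, and some early off-list events are covered by the immediate and six-month items.

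The part that does not stand is leaving the matter to the analysis plan. The protocol has not left the window open. It fixes day 8 in two places and contradicts it in others, so an analysis plan would inherit the conflict. Nor does Section 4.3.2 supply the missing definition: it names no unsolicited endpoint, and unlike the Synopsis it does not mention severity for these windows. Counting early off-list events only in the overall total also mixes them with common prompted reactions, where an unexpected pattern is harder to see.

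**Conclusion.** The protocol carries two incompatible definitions of its safety endpoint. Under the Synopsis and Table 1 of Section 4.2, unsolicited events begin at day 8. Under Sections 4.3.2, 4.5.1(1) and 10.3.4, events of all types count from day 0.

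The gap under the literal Synopsis wording is limited to events that are non-serious, not of special interest, off the solicited list, and start after 30 minutes and up to day 7. For these the named unsolicited incidence and severity would be incomplete. Total treatment-emergent incidence and its between-arm comparison would not be affected, and data capture is sound. The number of events concerned cannot be derived from the document.

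This rests on taking the Synopsis wording as written and on reading the other adverse events of Section 4.5.1(1) as unsolicited, which follows from their being whatever is not on the list. It is an endpoint-definition inconsistency that should be corrected, not a failure of the safety analysis as a whole.

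**What to change.** 1. In the Synopsis safety endpoint and in Table 1 of Section 4.2, define unsolicited adverse reactions and events over days 0-30. Keep solicited events at days 0-7.
2. Align Section 4.3.2, so that it names the solicited endpoint (days 0-7) and the unsolicited endpoint (days 0-30) and agrees with the Synopsis on whether severity is included.
3. In Section 10.3.4, state that the unsolicited summary uses the same days 0-30 window.
4. Add one sentence saying how a listed term that starts after day 7 is classed. Counting it as unsolicited would keep the present content of the days 8-30 endpoint unchanged, since Section 4.5.1(2) already collects any medical event in that period.

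The cost is wording and one changed table window. Section 4.5.1 already collects the events in both periods, so no visit, sample or form is added.
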